**Executive summary**

**Study Title**

**“Diaphragm dysfunction and peripheral muscle wasting in septic shock patients: exploring their relationship over time using ultrasound technology (the MUSiShock protocol)”**

**Short Title: MUS**i**S**hock - “Muscle Ultrasound Study in Shock Patient”

**Authors:** [name], [name], [name], [name], [name], [name], [name], [name]

**ethics approval and registration:** Swissethics - 2020-00452 / ClinicalTrials.gov - [NCT04550143](https://clinicaltrials.gov/ct2/show/NCT04550143)

**Study category and Rationale:** Research projects **not** classified as clinical trial.

**Category A (Swiss law – Human Research Act, HRA, and Human Research Ordinance, HRO) – “**Measures for sampling biological material or for the collection of personal data entail only minimal risks and discomfort”

 This is a prospective observational study intended to investigate muscle wasting in septic shock patients.

**Background and Rationale**

Intensive Care Unit (ICU) patients are known to lose muscle mass and function for many reasons, including prolonged immobilization, the effects of ICU treatments such as mechanical ventilation (MV) and the critical illness itself. Ultrasonography (US) is a bedside, radiation-free technology, widely used in the ICU setting. In the last two decades, new techniques have emerged in regard to its application for the assessment of the skeletal muscle (both limb and thoracic). It is a promising tool that may help detecting early changes in muscle structure and function. *MUSiShock* is a research project aiming to investigate structure and function of diaphragm and peripheral muscles using ultrasound techniques (Diaphragm US, DUS; Peripheral Muscle US, PMUS) in septic shock patients, and to assess their association with clinical outcomes such as the weaning from MV.

**Study design and schedule**

*MUSiShock* is single-centre, investigator-initiated, observational prospective cohort study, intended to investigate diaphragm and peripheral muscles (quadriceps *rectus femoris*) through the use of ultrasound techniques in septic shock patients. Participants will be assessed during their ICU stay. Recruitment period started in October/2020 and is intended to run for 24 months.

**Outcomes**

Primary outcome:

**1)** To characterize the association between Shear-Wave Elastography (SWE) and other US markers (thickness and thickness fraction for the diaphragm, echogenicity and cross-sectional area for the peripheral muscles).

As secondary outcomes:

**2.a)** The association between the changes in DUS and PMUS over time (between different times points and first assessment at ICU admission) will also be explored using change in all US markers.

**2.b)** The analysis of a combined model of one DUS marker and one PMUS marker (multiple combinations will be performed between all markers) to predict weaning success/failure will be performed as well.

**Eligibility**

| **Inclusion criteria** |  | **Exclusion criteria** |
| --- | --- | --- |
| - Adult patients (> 18 years old) admitted to the ICU, - With a diagnosis of septic shock, - A SOFA score equal to or greater than 8 points, at ICU admission, - Blood lactate concentration above 2 mmol/L at ICU admission, - Expected to have more than 48h of mechanical ventilation, - Expected to stay more than 5 days in the unit, by the attending physician, - Able to walk prior to ICU admission (walking aids accepted). |  | - Any underlying chronic disease leading skeletal muscle weakness/paralysis, - Pregnancy, - Lower limb amputation, fixators or open wounds, - Thoracic fixators or open wounds, - Being transferred from another ICU, - Sarcopenia or cachexia, - Palliative goals of care, - Intellectual or cognitive impairments, limiting the ability to follow instructions. |

**Recruitment Procedure**

All patients admitted to the study ICU will be screened within the first 24 hours after ICU admission; screening will be performed by investigators and the department’s research nursing team.

If eligibility conditions are met, participants (if awaken and able to collaborate) will be approached to provide informed consent within the first 24 hours. Then, data will start to be collected.

For participants not able to provide consent (the expected majority), with permission granted from the medical team in charge (a physician who is not participating in the research project, HRA, art. 30), data will be collected according to the study procedures. Participant’s consent (retrospectively) will be obtained as soon as patients regain capacity to provide consent.

In case of death or long-term disability impairing capacity to provide consent, the next of kin/legal representative will be asked to provide informed consent as soon as possible (HRO, art. 11).

**Measurements and procedures**

Study visits will be performed as follows:

- at **24 hours of ICU admission**
- **daily until day 5**, then
- **weekly** (at the end of every 7 days period),
- **at the extubation time**,
- at **ICU discharge**.

At each of these time points, we will assess quadriceps *rectus femoris* (RF) and diaphragm muscles (bilaterally), through PMUS and DUS measurements, respectively; while intubated and ventilated, the patient’s airway occlusion pressure (P0.1) will be monitored and recorded using the patient’s ventilator. In addition, for all time-points, patients’s ability to collaborate will be “checked” with “awakening” criteria by using the Standardized Five Questions (S5Q). If this ability to collaborate is confirmed, a Medical Research Council (MRC) sum score assessment will also be performed. Screening and assessments for each time-point will be performed without interfering with sedation/neuromuscular blocking agent medical administration.

**Number of Participants AND Rationale:** 84 participants.

For rationale, please see section “Statistical Considerations”, here bellow.

**Statistical Considerations:**

Changes over time in DUS markers, PMUS markers and MRC sum score will be explored using repeated-measures analysis of variance (ANOVA) or the Friedman test. For each time-point, association between different DUS or PMUS marker (DUS *versus* DUS or PMUS *versus* PMUS) will be analysed using *Pearson’s* or *Spearman’s Rank-Order* correlations tests; associations between DUS and PMUS (one DUS to one PMUS markers), will be assessed as well. Bland-Altman analysis will be performed to quantify the agreement (diagnostic accuracy) between US techniques for each structure.

In the prediction of weaning success and the presence of ICU-Acquired Weakness (ICUAW), logistic regression models will be performed taking into account the percentage of change (in relation to ICU admission values) and the absolute values of DUS markers alone, PMUS markers alone, and combined DUS and PMUS markers; these models will be adjusted for measured covariates (when available). Furthermore, discriminative power of all ultrasonographic techniques to detect weaning/failure will be assessed using Receiver Operating Characteristics (ROC) curves and Area Under the Curve (AUC) calculations.

Sample size estimation

For these analyses, we aim to be able to identify a linear correlation between the two US markers (SWE and one CMUS) and between the 2 muscles examined for each time-point. For that, we estimated a medium effect size of 0.30 for Pearson’s r, as proposed by Cohen. To reach the power to identify such an association with 80% power, an alpha level of 5% and a 2-sided test, we would need to include a minimum of **84 participants**.

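### Change in MRC sum score is assigned to complete-data tests, although the protocol's own rules probably leave that score missing in most patients at the first visit

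*Protocol*

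**What the plan says.** Statistical Considerations puts three kinds of measurement under one method: "Changes over time in DUS markers, PMUS markers and MRC sum score will be explored using repeated-measures" analysis of variance, with the Friedman test as the alternative. MRC gets no visits, time origin or method of its own.

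Measurements and procedures makes MRC conditional. Collaboration is checked at every time point "by using the Standardized Five Questions (S5Q"), and "If this ability to collaborate is confirmed, a Medical Research Council (MRC) sum score assessment will also be performed". Assessments take place "without interfering with sedation/neuromuscular blocking agent medical administration". The ultrasound measurements carry no such condition.

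Recruitment Procedure describes the patients expected at entry: "For participants not able to provide consent (the expected majority"), data collection starts with permission from a physician outside the project. Eligibility adds "Expected to have more than 48h of mechanical ventilation" and "Expected to stay more than 5 days in the unit".

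Visits fall at 24 hours, daily to day 5, weekly, at extubation and at ICU discharge.

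**The concern.** The method suits the ultrasound markers, which can be taken whether or not the patient is awake. It does not suit MRC, which exists only at visits where the patient is awake and cooperative. A patient lacking one of the analysed visits drops out of classical repeated-measures ANOVA or Friedman altogether, and the scores that patient did provide go too.

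The gaps are not random. Whether a score exists depends on sedation and, plausibly, on severity. The patients left would be those awake early and throughout, probably the less ill. The MRC course reported from them would not describe the cohort, and the early course could not be estimated for most patients at all.

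The same restriction may reach the models for ICU-acquired weakness (ICUAW). MRC is the only strength assessment among the listed measurements. If ICUAW is derived from it, ICUAW too can be seen only in patients who become assessable, and at differing times.

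**Working it through.** **1. The plan's own figure.** Inputs from Sample size estimation: r = 0.30, 80% power, two-sided alpha 5%. By Fisher's z,

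n = ((1.960 + 0.842) / atanh(0.30))² + 3 = (2.802 / 0.3095)² + 3 = 84.93, which rounds up to 85.

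A bias-corrected version with a t-based critical value gives 79.96% power at n = 84. The stated 84 therefore reproduces within rounding. It was built on ultrasound correlations and says nothing about how many patients will have MRC scores.

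**2. What the documents imply for the first visit.** A majority unable to consent means more than half of 84, so fewer than 84 × 0.5 = 42 are able, that is at most 41. Consent is sought within the first 24 hours and the first visit is at 24 hours, so the timing matches closely. Recruitment Procedure describes those approached for consent as awake and able to collaborate, and the S5Q check addresses the same capacity. The two are still not identical, so 42 is a proxy-based ceiling and not an exact count.

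**3. Range below the ceiling.** The protocol gives no awake rate. Treating the share able to collaborate at the first visit as an assumption, and requiring a series that starts there, the most patients who could enter are:

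| Assumed share awake at first visit | 84 × share | Approximate ceiling |
|---|---|---|
| 10% | 8.4 | 8 |
| 20% | 16.8 | 17 |
| 30% | 25.2 | 25 |
| 40% | 33.6 | 34 |
| 49% | 41.2 | 41 |

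Any later failed check, return to sedation or death lowers these numbers.

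**4. Starting later.** S5Q is repeated at every visit, so the ceilings in step 3 do not bind a series that begins at awakening. But such series do not line up. As an illustration, take four patients: one passes S5Q from the 24-hour visit onward, one first passes at day 5, one first passes at a weekly visit, and one dies without waking.

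- A complete-series test over the daily visits keeps only the first patient and discards every score from the second and third.
- A test over later visits excludes anyone not yet awake or already discharged, and ignores the earlier scores of those it keeps.
- A model that accepts incomplete series uses all scores from the first three. Neither approach says anything about the fourth.

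**The case against.** The strongest reply is that the protocol names no visits for MRC. Percentage change from ICU admission is specified for the ultrasound markers and not for MRC, so no admission MRC baseline is required. A comparison restricted to later visits, such as extubation and discharge, fits the text. The choice of visits and the handling of missing values commonly belong in a statistical analysis plan, which may exist. Missing MRC in uncooperative patients is also a declared feature of the design.

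Much of this stands, and absent missing-data detail is not criticised here. The reply does not rescue the named tests. Patients wake at different visits and stay for different times, so any fixed set of visits loses some patients and some usable scores. Realigning time to awakening would help, but the protocol does not say so, and series of unequal length would still have to be truncated for these two tests.

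Two stronger readings are tempting and not supported:

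- A reader might infer that the analysis has almost no usable cases. Eight or fewer would need both a first-visit awake share of about 10% or less and a series forced to begin at that visit. The documents fix neither.
- A reader might infer that the ICUAW models are unsound or will be presented as covering all septic shock patients. The protocol neither defines ICUAW nor states that it comes from MRC, and makes no such claim of scope.

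The objection is also right that a mixed model does not remove the restriction to patients who awaken. It recovers discarded scores; it does not create scores for patients who were never assessable.

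**Conclusion.** The point holds as a mismatch between a stated method and a conditionally observed outcome. Complete-data tests are named for MRC, while the protocol's own rules probably leave fewer than 42 of 84 patients with a first-visit score and let series start at different visits. Followed as written, the analysis would discard most partial MRC data and describe a selected group.

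This rests on three assumptions: that inability to consent stands in reasonably for failing S5Q at 24 hours; that repeated-measures ANOVA is meant in its classical complete-case form; and that patients awake early are on the whole less ill, which is plausible but not stated. The 8 to 41 range in the table depends on assumed awake shares and on starting at the first visit.

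The consequence is modest. The protocol calls this analysis exploratory, change in MRC is not listed under Outcomes, and the sample size does not depend on it. The correction is still worth making because it is cheap and uses data already being collected.

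**What to change.** - Remove MRC from the sentence assigning repeated-measures ANOVA or Friedman; this point does not affect the ultrasound markers there.
- Analyse all available MRC scores from each patient's first S5Q-positive visit, using a mixed model (or an ordinal longitudinal model) on time since awakening.
- Report the number assessed at each visit, and the number never assessable with reasons such as death or continued sedation.
- State that the MRC results apply to patients who become assessable. State the same for ICUAW if it is derived from MRC.

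The cost is a wording change, slightly more analysis work and a narrower conclusion. No new data are needed. Moving the time origin to awakening also changes the question, from the course since ICU admission to the course since the patient could first be tested, and the text should say so.

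### Repeated-measures ANOVA and the Friedman test fit a schedule with illness-driven follow-up poorly, so the muscle trajectory is at risk of selection bias after day 5 and for MRC

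*Protocol*

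**What the plan says.** The method is in the Protocol, under Statistical Considerations. Change in the ultrasound markers of both muscles, and in muscle strength by MRC, "will be explored using repeated-measures analysis of variance (ANOVA) or the Friedman test". No alternative is named, and the section does not say which visits enter the test.

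The schedule is in Measurements and procedures. There is a visit at 24 hours, then "daily until day 5", then weekly ("at the end of every 7 days period"), then "at the extubation time" and at "ICU discharge". Study design and schedule limits observation to the unit: "Participants will be assessed during their ICU stay". The MRC sum score is taken only when the awakening check shows that the patient can collaborate.

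Two other sections bear on who remains. Eligibility asks for an expected stay of more than 5 days, which is a forecast by the treating physician. Recruitment Procedure foresees deaths and expects most patients to be unable to consent at the start.

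**The concern.** Classical repeated-measures ANOVA and the Friedman test both work on a complete table of patients by time points. A patient with one empty cell among the visits analysed is removed altogether.

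This schedule cannot fill such a table for everyone:

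- The number of weekly visits depends on length of stay, which ends at discharge or death.
- Extubation and discharge are tied to events. They occur on different days in different patients and may coincide with a daily or weekly visit, so they are not levels of a common time factor.
- MRC is missing according to clinical state. Few patients are likely to have a complete early series, and those who do are the ones who were awake.

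Length of stay and survival are plausibly linked to muscle loss. If so, the patients with complete series are a selected group, and their mean change need not describe the cohort. The study title names the relationship of the muscles over time as its subject, so a distorted description of change would matter to readers even though the analysis is exploratory.

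**Working it through.** **The Protocol's own figure.** No figure is given for the analysis of change. The sample size of 84 rests on a Pearson correlation of 0.30, 80% power and two-sided alpha of 5%. By Fisher's z, n = ((1.960 + 0.842) / atanh 0.30)² + 3 = (2.802 / 0.3095)² + 3 = 84.9. With the bias term 0.30 / (2 × 83) added to atanh 0.30, n = 83.98. The 84 reproduces. It carries no stated allowance for missing visits.

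**Complete cases, scattered missing visits (assumed rates).** With a share m missing independently at each of T visits, 84 × (1 - m)^T patients are complete. Five visits are days 1 to 5, counting the 24-hour visit as day 1. Eight visits add days 7, 14 and 21.

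- m = 10%: 84 × 0.9^5 = 49.6; 84 × 0.9^8 = 36.2
- m = 15%: 84 × 0.85^5 = 37.3; 84 × 0.85^8 = 22.9

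**Complete cases, permanent departure (assumed rates).** Death and discharge remove a patient once and for all, so this form is closer to the concern.

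- Days 1 to 5, four intervals: 84 × 0.98^4 = 77.5 at 2% loss per day; 84 × 0.95^4 = 68.4 at 5%; 84 × 0.90^4 = 55.1 at 10%
- After three weekly visits, starting from 68.4: × 0.8³ = 35.0; × 0.7³ = 23.5; × 0.6³ = 14.8, for 20%, 30% and 40% loss per week

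**Bias (simulation, all inputs assumed).** There were 84 patients, visits at days 1, 2, 3, 4, 5, 7, 14 and 21, and a starting level of 100 (SD 8). The mean slope was -1 point per day (SD 0.5) and the residual SD was 4. Baseline loss was 2% per day to day 5, 5% to day 7, and 35% in each of the next two intervals. The true change is -4 at day 5, -13 at day 14 and -20 at day 21. The mixed model had a random intercept and slope.

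| Who leaves | Complete-case day 5 | Complete-case day 14 | Complete-case day 21 (patients) | Mixed model day 21 |
|---|---|---|---|---|
| Unrelated to wasting | -4.0 | -13.0 | -20.0 (31) | -19.7 |
| Less observed wasting leaves first | -4.3 | -15.3 | -25.8 (30) | -19.6 |
| More observed wasting leaves first | -3.7 | -10.7 | -14.2 (30) | -20.1 |
| Smaller underlying loss leaves first | -4.2 | -15.7 | -26.1 (33) | -23.3 |
| Larger underlying loss leaves first | -3.8 | -10.3 | -14.0 (33) | -17.0 |

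When discharge and death selected in opposite directions with equal strength, the complete-case mean at day 21 was -20.0 with about 25 patients. The bias cancelled, although few patients were left.

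**The case against.** The strongest reply is that the Protocol does not fix the visit set. A test on days 1 to 5 alone fits the wording, suits a cohort expected to stay longer than that, and in the simulation is off by less than 0.3 points. Which visits enter and how gaps are handled are often left to an analysis plan, which is not shown here. This stands as a limit on the size of the problem. It does not remove it, because the test itself is chosen in the Protocol, and any visit set that includes weekly visits or MRC loses patients for reasons tied to the course of illness.

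The analysis is also exploratory, and the mean trajectory is not itself a listed outcome. The correlations at each time point, the logistic models and the ROC curves do not need complete series, so this choice of test leaves them alone. That stands too.

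A reader might infer three stronger points that the documents do not support:

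- **That visits stop at extubation.** Extubation is one visit and ICU discharge is another. Only airway occlusion pressure is tied to ventilation: "while intubated and ventilated, the patient’s airway occlusion pressure (P0.1) will be monitored and recorded using the patient’s ventilator".
- **That the trajectory will be biased, in a known direction.** The Protocol gives no mortality, discharge or missing-visit rate and no link between wasting and leaving. The shift can go either way or be nil.
- **That the early change is badly distorted.** This takes a severe assumption. In one simulated scenario with 45 of 84 complete by day 5 and drop-out likelier in those losing more, the complete-case change was -6.1 against a true -10. That means losing (84 - 45) / 84 = 46% of patients within five days, which sits badly with the expected-stay criterion.

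**Conclusion.** The point holds as a risk. The named tests match the schedule poorly, and the trajectory is open to selection bias and loss of precision, chiefly after day 5 and for MRC.

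Under the assumed departure rates about 30 of 84 patients have a complete series to day 21, and the estimated change moves by about 6 points on a true -20 in either direction when leaving is tied to wasting. It does not move when leaving is unrelated to wasting or when opposing selections cancel. Within days 1 to 5 the bias is small if departures are few. Scattered missed visits can still cost many complete cases there (about 50 of 84 left at 10% per visit), but that is mainly a loss of precision if the misses are unrelated to wasting.

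Every rate and slope used here is an assumption. That both tests drop incomplete patients and that the schedule produces unequal follow-up do not depend on them. The change is worth making, but the primary outcome does not rest on it.

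**What to change.** Replace repeated-measures ANOVA and the Friedman test with a linear mixed model on all observed visits, with days since ICU admission as time and a transformation if the marker is skewed. Enter extubation and discharge values at their actual day or summarise them separately, not as further levels of time. Report how many patients are alive and in the ICU at each visit and, for MRC, how many could be assessed.

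Add one simple sensitivity analysis for death or discharge, such as trajectories by survival status. It is needed because the mixed model is no complete cure: when leaving depended on the unobserved slope, it gave -23.3 or -17.0 against a true -20.

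The cost is a change of wording, slightly more programming and an explicit modelling assumption about missing data. No new data are required.

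### Read literally, the within-diaphragm correlation tests pair thickness with thickness fraction, two markers that probably share a component, so a test against zero is unsafe for that pair

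*Protocol*

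**What the plan says.** The Outcomes section of the protocol gives the primary aim as "To characterize the association between Shear-Wave Elastography (SWE) and other US markers". For the diaphragm, the other markers are "thickness and thickness fraction for the diaphragm".

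The Statistical Considerations section then plans Pearson or Spearman tests, time-point by time-point, of the "association between different DUS or PMUS marker", with diaphragm markers set against diaphragm markers and limb markers against limb markers. No pair is excluded. With three diaphragm markers the pairs are SWE–thickness, SWE–fraction and thickness–fraction.

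The sample size has a different target. It aims to "identify a linear correlation between the two US markers (SWE and one CMUS) and between the 2 muscles examined for each time-point", with a "medium effect size of 0.30", 80% power, "an alpha level of 5% and a 2-sided test", giving "84 participants".

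The protocol never names the thickness–fraction pair. It gives no formula for the fraction, does not say at which phase of breathing the thickness marker is read, and gives no standard deviation or measurement error for either.

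**The concern.** A thickness fraction is built from thickness readings. If the fraction is (I − E)/E, with I the end-inspiratory and E the end-expiratory thickness, and the thickness marker is E, then a reading of E that is too high raises thickness and lowers the fraction in the same patient. The measured correlation is pushed below zero even when true fraction and true thickness are unrelated. If the thickness marker is I, the coupling pushes the correlation above zero. So even the direction of the effect depends on a choice that the protocol does not state.

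What is at stake is interpretation. A significant negative correlation could be reported as thinner diaphragms contracting more when part or all of it comes from the arithmetic. The test is repeated at every visit (24 hours, daily to day 5, weekly, extubation, ICU discharge), so the same bias would recur and could be mistaken for replication.

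**Working it through.** **1. The plan's own figure.** For r = 0.30, 80% power and two-sided 5%, Fisher's z gives n = ((1.960 + 0.842)/atanh(0.30))² + 3 = (2.802/0.3095)² + 3 = 84.93. The stated 84 therefore reproduces to within one patient. Power at 84 is 79.6% by Fisher's z and 81.3% by the noncentral t. The sample size is not in question here.

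**2. Inputs for the coupled pair.** Only n = 84 and the two-sided 5% level come from the protocol. Everything else is assumed: fraction = (I − E)/E; thickness marker = E; mean E 2.0 mm, SD 0.4 to 0.6 mm; true fraction 25%, SD 10 points, independent of true E; reading error SD σ from 0 to 0.20 mm on both I and E, with error correlation ρ of 0 or 0.8.

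**3. Direction and rough size by hand** (SD of E 0.5 mm, σ = 0.10 mm). To first order:

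- Covariance induced by error ≈ σ²(ρ − 1.25)/2.0. For ρ = 0: 0.01 × (−1.25)/2.0 = −0.00625.
- Variance of the measured fraction ≈ 0.10² + σ²(1 − 2.5ρ + 1.25²)/2.0². For ρ = 0: 0.01 + 0.01 × 2.5625/4 = 0.0164, so SD 0.128.
- SD of measured E = √(0.25 + 0.01) = 0.51.
- Induced r ≈ −0.00625/(0.51 × 0.128) ≈ −0.10. Simulation gives −0.11.

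For ρ = 0.8 the covariance is 0.01 × (−0.45)/2.0 = −0.00225, the variance is 0.01 + 0.01 × 0.5625/4 = 0.0114 (SD 0.107), and r ≈ −0.00225/(0.51 × 0.107) ≈ −0.04. With σ = 0 the induced covariance is zero.

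**4. Rejection rate of the nominal 5% Pearson test** (simulated studies of n = 84; ranges are over SD of E 0.4 to 0.6 mm):

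| Error SD | Independent errors | Errors correlated 0.8 |
|---|---|---|
| 0 mm | about 5% | about 5% |
| 0.05 mm | 7% to 8% | about 5% |
| 0.10 mm | 19% to 24% | about 9% |
| 0.20 mm | 64% to 83% | 31% to 39% |

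With independent errors, mean r is −0.10 to −0.13 at 0.10 mm and −0.26 to −0.32 at 0.20 mm. The latter is close in size to the 0.30 that the study is powered to detect.

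**5. Does Spearman help?** With SD of E 0.5 mm, fraction SD 12 points and independent errors, Pearson against Spearman is 18% against 12% at 0.10 mm, and 69% against 54% at 0.20 mm. Ranks reduce the problem but do not remove it.

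**6. If the thickness marker is end-inspiratory.** Then I = E(1 + F), where F is the fraction. With F independent of E and no error, cov(I, F) = 2.0 × 0.10² = 0.02. Var(I) = (2.0² + 0.5²)(1.25² + 0.10²) − 2.5² = 4.25 × 1.5725 − 6.25 = 0.433, so SD 0.658. Hence r = 0.02/(0.658 × 0.10) ≈ +0.30. With measurement error the simulated value is about +0.25 to +0.27, and 61% to 69% of studies reject. This coupling is structural and does not need measurement error.

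**7. Opposite-side pairing.** Both sides are scanned, so thickness from one side can be set against the fraction from the other. With a side-to-side thickness correlation of 0.85 (assumed) and fraction independent of thickness, rejection falls to roughly 5% to 10%. If instead the absolute increment I − E is unrelated to thickness (assumed 0.5 mm, SD 0.2 mm, common to both sides), opposite-side testing still rejects in 52% to over 99%. It removes most of the shared error but not the structural coupling.

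**The case against.** The strongest reply is that the pair is never named. The primary outcome is SWE against the other markers, the sample size rests on SWE and on the two muscles, and the diaphragm-against-diaphragm wording can be read as simply delivering the SWE comparisons. Definitions of the fraction and of the thickness marker may also stand in documents not at hand. This keeps the point small and means the absent formula is not itself a fault. It does not take the pair out of a sentence that excludes none.

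Three stronger readings are tempting, and the documents do not support them.

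- *The false-positive rate is certainly badly inflated.* A ratio correlated with its denominator does not by itself break the 5% level. With negligible error and a fraction independent of end-expiratory thickness, the test holds about 5%. The inflation depends on the formula, the marker, the size and correlation of the errors, and any averaging of readings, none of which the protocol gives.
- *Near-certain rejection when the absolute increment is unrelated to thickness shows a false-positive rate.* In that case the fraction truly is lower in thicker diaphragms. Rejecting zero is correct, and only the physiological reading is delicate.
- *Correlations between changes in the two markers share the fault.* No such correlation is planned. Secondary outcome 2.a relates diaphragm changes to limb-muscle changes, and the within-diaphragm correlations are set for each time-point.

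**Conclusion.** The point holds in a limited form. As written, the plan tests thickness against thickness fraction, and for that one pair zero is not a dependable null value. Under the stated assumptions with an end-expiratory marker, the actual level of the 5% Pearson test runs from no inflation, through 9% to 24% at 0.10 mm error, to 31% to 83% at 0.20 mm, depending on how strongly the paired errors correlate. An end-inspiratory marker would reverse the sign. All inputs except n and the nominal level are assumed, so these figures show what can happen and do not estimate what will. The primary outcome, the sample size and the weaning models are untouched. This is a cheap improvement to a secondary analysis.

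**What to change.** Add one sentence to the Statistical Considerations section: the diaphragm thickness against thickness-fraction pair is excluded from the correlation tests against zero and is reported descriptively (scatter plot and coefficient, without a p-value), with a note that the two markers are coupled. The same sentence should name the formula for the fraction and the thickness marker used.

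Opposite-side pairing can be shown as a sensitivity display at most, for the reason in step 7.

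No new data are needed and the other planned correlations stay as they are. The cost is that one exploratory pair loses its p-value.
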